### Statistical analyses

Baseline characteristics will be presented using descriptive statistics; continuous data will be summarized as mean and standard deviation in case of normal distribution, or as median and range when distribution is skewed. Categorical data will be presented a frequencies and proportions.

The primary analysis will be performed on the main outcome measure of this study, the Karlsson score, at 6 months follow-up. The treatment groups will be compared using an ANOVA test with post hoc pairwise comparisons (with Bonferrini correction). The adjusted confidence intervals from these contrasts will be used to test for non-inferiority using the prespecified non-inferiority margin.

Due to the repeated datastructure, secondary analyses will be performed using linear mixed models on the Karlsson score, FAOS score and VAS scores (change from baseline) to estimate change as a function of time and mean differences between the treatment groups. Akaike Information Criteria (AIC) will be used as an indicator for model fit. The number of recurrent ankle injuries and adverse events will be analyzed using a *X*^2 ^test or log-rank test, when appropriate. Analyses will be based on the intention-to-treat principle and performed in PASW statistics 18 (SPSS Inc. Chicago, IL). Statistical uncertainty will be quantified by 95% confidence intervals.

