**Figure 1 F1:**
[figure not shown]
**ANKLE TRIAL flow chart (inclusion, randomization and follow-up)**.

**Table 1 T1:** Follow-up moments and outcome measurement

	VAS pain	Karlsson	FAOS	VAS satisfaction	Number of recurrences
< 24 h	+	-	-	-	-

5-7 days	+	+	+	-	-

6 weeks	+	+	+	-	+

6 months	+	+	-	+	+

1 year	+	+	+	+	+

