### Sample size

To prove the hypothesis, the required number of patients was estimated using a sample size analysis, calculated with the contingent primary outcome variable Karlsson scoring scale, according to a study of Boyce et al. [29]. Sample size calculation for this non-inferiority study was based on 3 post hoc comparisons with Bonferroni adjustment. Therefore a one-sided α-level of 0.025/3 = 0.008 was chosen. Limits of equivalence were set at 10 points of the Karlsson score and an expected difference of zero. Based on a standard deviation of 15 and power of 80%, we estimate that 50 patients per group are minimally necessary. With correction of 15% of expected patients to drop out we will include in our study 60 patients per group and 180 patients in total.

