### Randomization and blinding

Physicians at the emergency department of both Jeroen Bosch hospital, 's-Hertogenbosch, The Netherlands and Slotervaart Hospital, Amsterdam, The Netherlands will recruit patients. Using the same study protocol for both hospitals, the physician will inform patients, who meet the inclusion criteria, about the study. The selected patients will also receive a brochure with written patient information. To avoid selection bias, only after they have signed informed consent, patients will be allocated to one of the three treatment strategies using a web-based computer randomization tool. Independent and qualified plaster nurses will be responsible for follow-up and data collection of the case record forms after 5-7 days and after 6 weeks. FG will collect data out of the case record forms and will put them into a database (not blinded). SW finally will analyze this objective database.

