## Discussion

The ANKLE TRIAL is a randomized controlled trial in which a purely functionally treated (control) group, without any form of external support, will be investigated and compared with two external support treatment (intervention) groups. Recruitment of patients in Jeroen Bosch Hospital has started since January 2010 and in Slotervaart Hospital since July 2011. Recruitment will be finished when 180 patients have been included, which we expect will be at the end of 2011. We expect to publish initial results of our study in 2013.

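### The primary ANOVA carries treatment only; prespecifying hospital, and first-day VAS pain if taken before allocation, would be a cheap and probably modest efficiency gain

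*Protocol article*

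**What the plan says.** Under Statistical analyses, the primary endpoint is "the Karlsson score, at 6 months follow-up", and "The treatment groups will be compared using an ANOVA test", followed by Bonferroni-corrected contrasts between pairs of groups. The intervals from these contrasts, adjusted for multiplicity, are then compared with the non-inferiority margin. The word adjusted refers there to Bonferroni only. The linear mixed models are secondary, and no centre term is named for them either.

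Under Sample size, "a one-sided α-level of 0.025/3 = 0.008 was chosen" and "Limits of equivalence were set at 10 points of the Karlsson score and an expected difference of zero", with SD 15, 80% power, 50 evaluable patients per group and 60 recruited to allow for 15% dropout.

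Two candidate covariates are already to hand:

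- **First-day VAS pain.** Table 1 ("Follow-up moments and outcome measurement") marks VAS pain as the only measure in the row for the first 24 hours. Karlsson and FAOS scores start at 5-7 days, the visit that Trial design labels baseline.
- **Hospital.** Two hospitals recruit. The Discussion dates the first from January 2010 and the second "in Slotervaart Hospital since July 2011", with completion expected at the end of 2011.

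Under Randomization and blinding, patients are "allocated to one of the three treatment strategies using a web-based computer randomization tool". Stratification by hospital is neither stated nor excluded.

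**The concern.** Outcome variation that hospital or initial pain could explain stays in the error term of a treatment-only ANOVA. It widens the very intervals on which the non-inferiority decision rests. The design has little slack: 50 evaluable patients per group are needed and 60 × 0.85 = 51 are expected.

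The second hospital opened 18 months after the first and would recruit for about 6 of 24 months. If it supplies a minority of patients and allocation is not stratified, its patients may by chance be spread unevenly over the arms. A treatment-only model leaves any resulting shift in the contrast.

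There is also a practical hazard. Someone who later decides to adjust for baseline could take the label in Trial design literally and use the 5-7 day Karlsson score. By then the arms have already been treated differently, with pressure bandage in two groups and none in the third (Interventions). Naming the covariates in advance prevents that, and it prevents a data-driven choice.

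**Working it through.** **Inputs from the article.** Margin 10, true difference 0, SD 15, one-sided α = 0.025/3 = 0.00833, power 80%, 60 per group, 15% dropout.

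**Assumed, because not given.** R, the multiple correlation of hospital and first-day VAS pain with the 6-month Karlsson score (0 to 0.4); the second hospital's share of patients (10% to 33%); the mean difference between hospitals (5 to 10 points).

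**1. The plan's own figure.** By the normal approximation, n = 2 × [15 × (2.394 + 0.842)/10]² = 47.1, so 48 per group. The noncentral t gives 49 or 50, depending on whether α is rounded to 0.008. The stated 50 is reproduced, and 50/0.85 = 58.8 supports recruiting 60.

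**2. Unadjusted power at 51 per group.** The standard error of a contrast is 15 × √(2/51) = 2.97. The noncentrality is 10/2.97 = 3.37 on 3 × 51 − 3 = 150 degrees of freedom. Noncentral-t power is 82.6% per comparison.

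**3. Adjusted power at 51 per group.** The residual SD is 15 × √(1 − R²). Two covariate terms leave 148 degrees of freedom and inflate the variance by about (1 + 2/148). The last column omits that inflation, which would widen each half-width by less than 1%.

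| R (assumed) | Residual SD | Power, adjusted | Change from 82.6% (points) | CI half-width, points |
|---|---|---|---|---|
| 0 | 15.00 | 82.1% | about −0.6 | 7.19 |
| 0.1 | 14.92 | 82.5% | about −0.1 | 7.16 |
| 0.2 | 14.70 | 83.8% | +1.2 | 7.05 |
| 0.3 | 14.31 | 85.9% | +3.3 | 6.86 |
| 0.4 | 13.75 | 88.9% | +6.3 | 6.59 |

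The loss at R = 0 is 82.65% − 82.06% = 0.59 points before rounding. Break-even lies near R = 0.1. A normal approximation that ignores the covariates' cost would show a small gain there (83.9% against 83.5%), which disappears once the cost is charged.

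**4. Chance imbalance between hospitals.** Under simple randomisation with 60 per arm, the difference between two arms in the second hospital's share p has SD √(2p(1 − p)/60).

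- p = 0.10: SD 0.055, 95% range ±1.96 × 0.055 = ±0.107
- p = 0.33: SD 0.086, 95% range ±1.96 × 0.086 = ±0.168

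Multiplying by the hospital difference gives the 95% limit of the shift in a contrast. For a 5-point difference it is 0.54 to 0.84 points; for a 10-point difference it is 1.07 to 1.68 points. In most randomisations the shift would be smaller.

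**The case against.** The strongest reply is that nothing is wrong. A treatment-only ANOVA is valid under randomisation, it is the analysis the sample size assumes, and it gives about 83% power against a planned 80%. That stands, and it limits this point to an optional improvement.

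Several further objections also stand:

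- **The prognostic strength is unknown and may be low.** The Background says that pain in the acute phase is a poor pointer to serious injury. That concerns diagnosis and not the 6-month score, so it is indirect, but it gives no reason to expect R of 0.3 or more.
- **Adjustment is not free.** It costs two degrees of freedom, about 0.6 power points if neither variable is prognostic, and a rule for missing VAS values.
- **The timing of the VAS is not settled.** Table 1 says only that it falls within 24 hours. Nothing places it before allocation, the trial is open, and the groups differ in bandaging from the start.
- **Silence on stratification proves little.** The text is a condensed article, and the full protocol may specify it.

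A reader might also infer that the late opening of the second hospital biases the comparison. The article does not support that: patients are randomised at both hospitals under a common protocol, so calendar time and centre are not confounded with arm. Nor would a centre term remove an imbalance; it corrects the estimate for it.

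What the objections do not remove is that the article states the primary model, that the model leaves out information already collected, and that using this information takes one prespecified line.

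**Conclusion.** The point holds as an efficiency recommendation of low severity. The planned analysis is valid, and a reading that it is biased or underpowered is not supported.

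The benefit cannot be fixed from the article. It ranges from a loss of about 0.6 power points at R = 0, through about +1 at 0.2 and +3 at 0.3, to about +6 at 0.4. These figures rest on the article's SD of 15, a true difference of zero, 51 evaluable patients per group and an assumed R. The centre correction is worth at most about 0.5 to 1.7 points at the 95% limit, assuming unstratified allocation, a second-hospital share of 10% to 33% and a hospital difference of 5 to 10 points. That is small beside the 10-point margin, but it could matter for an interval that ends close to it.

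The case for hospital is unconditional. The case for VAS pain depends on its being recorded before allocation.

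**What to change.** Before the data are analysed, prespecify the primary comparison as an ANCOVA of the 6-month Karlsson score, with treatment and hospital as fixed factors and first-day VAS pain as a linear covariate. Keep the Bonferroni-corrected contrasts and the margin as they are. Attach three conditions:

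1. Confirm from the case record form that the first-day VAS is taken before allocation. If it is not, or if this cannot be shown, adjust for hospital alone.
2. State that the 5-7 day scores are not used as covariates in the primary model, because they follow randomisation despite being called baseline.
3. State how missing VAS values are handled, so that no patient leaves the primary analysis for want of a covariate.

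Report the unadjusted ANOVA as a sensitivity analysis. If the full protocol does stratify allocation by hospital, the centre term belongs in the model for that reason as well.

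The cost is one line of text, two degrees of freedom and no new data. The sample size need not change.

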## Background

### Meaning and diagnosis of ankle injuries

Injury to the lateral ligament complex of the ankle is the most common injury in many sports. About one quarter of all injuries across all sports are ankle injuries. In the United States about one sprain per 10.000 people occur per day, in the Netherlands an annual total of 234.000 ankle sprains caused by sports activities are registered [1,2]. Of these, 47% require some form of medical treatment which leads to an estimated annual cost of more than € 80.000.000, only in the Netherlands [3].

Traditionally, the diagnosis of ankle sprain is based on history and delayed physical examination, 5-7 days after initial trauma [4]. The most common injury mechanism is supination and adduction (called inversion) with the foot plantar flexed. Any additional X-rays are used only to exclude other diagnoses, such as a fracture or disturbance of the joint congruency, based on the Ottawa ankle rules [5].

To determine an apparent rupture, a repetition of the physical examination a few days later is more valid [4]. It is hard to distinguish a rupture (grade II/III ankle injury) from a simple sprain (grade I ankle injury) in the first couple of days after injury, because pain, swelling and muscle tension complicate interpretation of the physical examination. In addition, both swelling and pain have a limited positive predictive value for serious injury in the acute phase. The distinction between a grade I or grade II/III injuries is important because of consequences for both treatment and prognosis. It is suggested that a sprain (grade I ankle injury) does not need any treatment because "functional instability" or recurrent sprain is less frequent after ligament sprains than after ligament ruptures [6].

Generally, the prognosis of ankle injuries is good, whatever treatment is followed [7]. Zeegers has showed that at least 80% of patients in all compared treatment groups were free of complaints after one year [8]. However, there is still potential for improvement in 20% of these patients.

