### Trial design

The ANKLE TRIAL is designed as a prospective open randomized multi-centre trial with a one-year follow-up in which we compare three different functional treatment strategies of acute ankle sprains. A residual-free healing and prevention of chronic symptoms and functional instability will be pursued. Therefore, results during follow-up primarily will be evaluated with a statistically validated scoring scale, which measures ankle joint function in the rehabilitation phase after acute ligament injury, according to Karlsson and Peterson [25]. In this scale a maximum of 90 points can be given in following categories: pain (20), swelling (10), instability (subjective) (15), stiffnes (5), stair climbing (10), running (10), work activities (15), and use of support device (5). Selected patients will be randomized in three treatment groups, as showed [Figure 1] with an allocation ratio of 1:1:1. For follow-up patients will return to the hospital after five to seven days (baseline), after six weeks and after one year. After six months patients will be contacted by telephone [Table 1].

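### The non-inferiority intervals rest on ANOVA contrasts that normally pool one variance over three arms; on a score capped at 90 a worse no-support arm may be more variable, so separate-variance intervals are a cheap safeguard

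*Protocol article*

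**What the plan says.** The Statistical analyses section sets the primary analysis on the Karlsson score at 6 months: "The treatment groups will be compared using an ANOVA test with post hoc pairwise comparisons (with Bonferrini correction"). The decision rule follows: "The adjusted confidence intervals from these contrasts will be used to test for non-inferiority using the prespecified non-inferiority margin". No variance estimator is named, and no unequal-variance alternative is given for this analysis. Skewness is mentioned only for the description of baseline data.

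The Sample size section supplies the planning figures:
- Contrasts: "Sample size calculation for this non-inferiority study was based on 3 post hoc comparisons with Bonferroni adjustment".
- Level: "Therefore a one-sided α-level of 0.025/3 = 0.008 was chosen".
- Margin: "Limits of equivalence were set at 10 points of the Karlsson score and an expected difference of zero".
- Variability and size: "Based on a standard deviation of 15 and power of 80%, we estimate that 50 patients per group are minimally necessary".

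A single SD of 15 is thus used for every arm. The Trial design section fixes allocation at 1:1:1 and describes the scale: "In this scale a maximum of 90 points can be given in following categories". The Background (Meaning and diagnosis of ankle injuries) cites an external study in which "at least 80% of patients in all compared treatment groups were free of complaints after one year".

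**The concern.** A one-way ANOVA followed by Bonferroni contrasts ordinarily uses one mean square error for every pair. That is sound when the three SDs are equal. On a score with a ceiling, equality is least secure where it matters most for non-inferiority, namely when one arm is truly worse by the margin. If that deficit arises because fewer no-support patients recover fully, scores leave the ceiling and spread out, and the SD of that arm rises. The two less variable device arms then pull the pooled variance below what the no-support contrasts need.

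Equal arm sizes do not repair this. With two arms of equal size, the pooled and separate-variance standard errors coincide. With three arms, the arm outside the contrast also enters the pooled variance.

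At stake is the false-claim rate at the 10-point margin. An interval that is too narrow favours the hypothesis that external support adds nothing. The tape-versus-brace interval would be too wide instead.

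**Working it through.** **1. The plan's own figure.** Inputs from the Sample size section: margin 10, SD 15, true difference 0, one-sided level 0.025/3 = 0.00833, power 80%.

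n per arm = 2 × [15 × (2.394 + 0.842)/10]² = 47.1, so 48. The noncentral t distribution gives 49, or 50 if the level is rounded to 0.008 with two-arm degrees of freedom. The stated 50 is reproduced. Dropout: 50/0.85 = 58.8, so 59 against the stated 60; conversely 60 × 0.85 = 51 analysed per arm.

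**2. Effect of unequal SDs (normal approximation, n = 50 per arm).** Assume both device arms have the planned SD of 15 and the no-support arm has SD 15r. The article does not give r.

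- Pooled SE² = (2/n) × 15² × (2 + r²)/3
- True SE² of a no-support contrast = 15² × (1 + r²)/n
- k = pooled SE/true SE = √[2(2 + r²)/(3(1 + r²))]
- Actual one-sided error = 1 − Φ(2.394 × k)

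Example, r = 1.25: r² = 1.5625, k = √(7.125/7.6875) = 0.963, error = 1 − Φ(2.305) = 0.0106.

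| r | k | Error per contrast | Joint error, two no-support contrasts | Half-width, pooled vs correct (points) |
|---|---|---|---|---|
| 1.00 | 1.000 | 0.0083 | 0.0157 | 7.27 vs 7.27 |
| 1.25 | 0.963 | 0.0106 | 0.0191 | 7.92 vs 8.22 |
| 1.33 | 0.953 | 0.0113 | 0.0201 | 8.14 vs 8.55 |
| 1.50 | 0.934 | 0.0127 | 0.0219 | 8.65 vs 9.26 |
| 2.00 | 0.894 | 0.0161 | 0.0257 | 10.27 vs 11.49 |

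Here the joint error is the chance of at least one false claim when no support is worse than both devices by exactly 10 points. The tape-brace interval is too wide by the factor √[(2 + r²)/3]: 1.09 at r = 1.25 and 1.19 at r = 1.5.

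**3. What SD ratio might a ceiling at 90 produce?** This depends on the assumed 6-month mean and on how the deficit arises. Simulation used 50 per arm, normal scores capped at 90, device SD 15 and no support 10 points worse:

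| Device mean (assumed) | SD ratio | Pooled, per contrast | Welch, per contrast | Pooled, joint | Welch, joint |
|---|---|---|---|---|---|
| 60 | 1.02 | 0.0083 | 0.0081 | 0.0152 | 0.0147 |
| 70 | 1.09 | 0.0087 | 0.0079 | 0.0164 | 0.0146 |
| 75 | 1.17 | 0.0099 | 0.0081 | 0.0181 | 0.0146 |
| 80 | 1.34 | 0.0118 | 0.0087 | 0.0216 | 0.0154 |
| 82 | 1.46 | 0.0139 | 0.0101 | 0.0249 | 0.0170 |

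**4. Two ways to be 10 points worse.** Suppose 80% of device patients score 90 and 20% score 52.5. The mean is 82.5 and the SD is 37.5 × √(0.2 × 0.8) = 15.

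- More patients with residual complaints: the share at 52.5 becomes 0.2 + 10/37.5 = 0.467, and the SD is 37.5 × √(0.467 × 0.533) = 18.7, ratio 1.25. Simulated error per contrast: pooled 0.0097, Welch 0.0069. Joint, pooled: 0.0179.
- Every patient 10 points lower: mean 72.5, SD still 15. Simulated pooled error 0.0085, essentially nominal.

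So the ceiling allows a larger SD but does not force one.

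**5. Limit of the remedy.** In an extreme case the same 20% fall to 2.5 (SD 35). Pooled error per contrast is then 0.0305, and Welch still gives 0.0215. Separate variances do not remove the part that comes from skewness.

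**The case against.** The strongest reply is that nothing in the article is shown to be wrong. ANOVA with Bonferroni contrasts is conventional. Pooling is inferred from that description rather than stated, and a condensed article may leave the standard error to a fuller document. This stands as a reason for modest weight. The article does, however, name the method behind its primary decision, and the ordinary form of that method pools.

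A reader might infer that an arm worse by the margin must have a larger SD. The documents do not support that: a uniform 10-point fall leaves the SD at 15, and with a device mean near 60 the ratio is only 1.02. A reader might also infer that the trial expects most patients at the ceiling at 6 months. The 80% figure comes from a cited study, refers to one year and concerns freedom from complaints, not 90 Karlsson points. The article gives no expected Karlsson mean.

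On size, larger error rates can be generated, for example by assuming that 90% or 95% of device patients are fully healed. Those settings abandon the planned SD of 15: with scores of 90 or 50, the device SD becomes 40 × √(0.9 × 0.1) = 12 or 40 × √(0.95 × 0.05) = 8.7. Held at SD 15 with a ratio of 1.25, the half-width is only about 0.3 points too small against a 10-point margin. Because the level is split over three contrasts and only two involve no support, their joint error then remains under 2.5%. If the claim needs non-inferiority to both tape and brace, its error cannot exceed that of one contrast. All of this stands.

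**Conclusion.** The point holds as a conditional one. If the contrasts are computed in the usual pooled form and the no-support arm is the more variable, both of its intervals are too narrow despite equal allocation, in the direction that favours the trial's hypothesis. A score bounded at 90 makes such a difference in SD plausible, not certain.

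The size rests on assumed SD ratios. At 1.25 to 1.5 the intervals are about 4-7% too narrow and the per-contrast error is about 1.1-1.3% instead of 0.83%. The joint error over the two no-support contrasts reaches 2.5% only at a ratio of nearly 2 under normality, or about 1.45 in the skewed, capped simulation. It would be wrong to conclude that the plan's overall error control fails: with the SD near 15 and moderate ratios it does not. The sample size of 50 per group is unaffected under its own equal-SD assumption. This is a low-cost improvement to the analysis, not a proven error.

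**What to change.** Keep the three contrasts, the 10-point margin and the Bonferroni level. Add one sentence to the Statistical analyses section: each 98.33% interval (two-sided, equivalent to one-sided 0.025/3) is computed with separate arm variances, of Welch-Satterthwaite or Games-Howell type. If the contrasts come from a regression model, use heteroscedasticity-robust standard errors.

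The cost is small. With equal SDs and 51 analysed per arm, the degrees of freedom fall from 150 to about 100 and the critical value rises from 2.421 to 2.435 (0.6%). Power goes from 82.6% to 82.2%, so no more patients are needed. Under strong skew the correction is only partial, as shown above.

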### Participants

Adult and healthy patients with acute (within 24 h), single sided and first inversion trauma of the lateral ankle ligaments will be eligible for inclusion. Patients will be excluded if they do not master the Dutch language, if they are low ambulatory or if there is another (or secondary) diagnosis than lateral ankle sprain (e.g. fracture of the ankle). If necessary, × rays will be performed to exclude ankle fractures, according to the Ottawa ankle rules. All lateral ankle ligament injuries will be included, regardless of severity, as in the acute stage it is hard to distinguish between. After 5-7 days, following the case record form, a delayed physical examination according to Van Dijk [4] will take place and function scores according to De Bie et al. [26] will be determined. From here we can distract the severity of the injuries, which will be important for sub analysis.

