### Interventions

The first treatment group will receive pressure bandage and RICE (Rest, Ice, Compression, Elevation) therapy for 5 to 7 days followed by tape treatment for 6 weeks, the second group will be treated by pressure bandage and RICE therapy for 5 to 7 days followed by brace treatment for 6 weeks and the third group RICE therapy and purely functional treatment. The last group will not be given pressure bandage or external support, except for an elastic sock if desired.

In addition, patients in all three groups will receive the same ankle exercise schedule, based on regular existing physiotherapy protocols [Table 2]. Only the first two days after the inversion trauma patients (of all groups) are allowed to take Paracetamol for pain relieve as necessary. After two days they can start weight bearing guided by pain.

**Table 2 T2:** Stepwise exercise schedule with training modality accents per phase

	Training Modalities							
**Step**	**Time**	**N***	**Range of motion**	**Weight bearing**	**Walking**	**Stretching**	**Strength**	**Balance**

1	0-2 days	1-3	+++	minimal	-crutches	-	-	-

2	3-10 days	4-6	+	+	+ guided by pain			

3	11-21 days	7-10	++	++	++ incl running	+	+	++ one leg standing

4	3-6 weeks	11-14	++	++	++	+	++	+++

* Number of exercises

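### The secondary mixed models subtract a 'baseline' score taken after a week of differing randomised treatment, so their comparisons with the no-support group lose any first-week difference

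*Protocol article*

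**What the plan says.** The Statistical analyses section plans that "secondary analyses will be performed using linear mixed models on the Karlsson score, FAOS score and VAS scores (change from baseline"). The models are meant to estimate both the course over time and the mean differences between groups. The primary analysis, in the same section, is an ANOVA of the Karlsson score at 6 months and is not described as a change score.

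Baseline is given a meaning in one place only, under Trial design: "For follow-up patients will return to the hospital after five to seven days (baseline), after six weeks and after one year". The same sentence calls that visit follow-up and baseline at once.

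The timing of entry and treatment is as follows:

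- **Entry (Participants):** "Adult and healthy patients with acute (within 24 h), single sided and first inversion trauma".
- **Allocation (Randomization and blinding):** emergency department physicians recruit, and "only after they have signed informed consent, patients will be allocated to one of the three treatment strategies using a web-based computer randomization tool".
- **First week, group 1 (Interventions):** "The first treatment group will receive pressure bandage and RICE (Rest, Ice, Compression, Elevation) therapy for 5 to 7 days followed by tape treatment". Group 2 has the same first week and then a brace.
- **First week, group 3 (Interventions):** RICE, and "The last group will not be given pressure bandage or external support, except for an elastic sock if desired".

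Table 1 gives the measurements. Only VAS pain is recorded at <24 h. Karlsson and FAOS are first recorded at 5-7 days. VAS satisfaction is recorded only at 6 months and 1 year.

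**The concern.** A baseline that is subtracted from later scores has to be free of the treatment being compared. The 5-7 day score is not. It is recorded after allocation, at the end of a period in which the arms are deliberately treated differently, and the Abstract names the pressure bandage as part of the tape and brace strategies. Subtracting it removes whatever the first week did from each later comparison with group 3, and that is the comparison the hypothesis is about.

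Within this article, the 1-year Karlsson comparison, the FAOS comparisons at 6 weeks and 1 year, and the VAS pain comparisons rest on these models, with no raw-score analysis named beside them. At 6 months the secondary Karlsson result could differ from the primary ANOVA for purely arithmetical reasons, and a reader would have no way of telling that from a real inconsistency.

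The VAS rule has two further faults. Satisfaction has no value before 6 months, so a change from baseline cannot be formed. Pain has a <24 h value, but the only visit labelled baseline is the later one.

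**Working it through.** **1. The plan's own figure.** The point rests on no stated number, but the sample size shows what is not affected. Inputs from Sample size: margin 10, SD 15, expected difference 0, one-sided alpha 0.025/3, power 80%.

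n per group = 2 × [SD × (z for alpha + z for power) / margin]² = 2 × [15 × (2.394 + 0.842) / 10]² = 2 × 4.854² = 47.1, so 48. With the t distribution, 49 per group gives 80.4% power and 50 gives 81.3%. The stated 50 reproduces. Dropout: 50 / 0.85 = 58.8, so 59, against the stated 60. These figures belong to the primary comparison and do not involve the day 5-7 score.

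**2. The change-score contrast.** Let d1 be the mean difference (group 1 or 2 minus group 3) at 5-7 days and dL the same difference at a later visit. Then

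expected change-score contrast = dL - d1.

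The bias against the later difference is -d1, whatever the correlation between visits.

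**3. Illustration.** The documents give no first-week effect, so all d1 and dL values are assumed, in Karlsson points. Simulation used 50 per group, SD 15, 4,000 trials per setting and assumed correlations of 0.3, 0.5 and 0.7:

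| d1 | dL | dL - d1 | Simulated change contrast (0.3 / 0.5 / 0.7) | Simulated raw later difference (0.3 / 0.5 / 0.7) |
|---|---|---|---|---|
| 0 | 0 | 0 | 0.00 / 0.04 / -0.06 | 0.02 / 0.07 / -0.03 |
| 2 | 0 | -2 | -2.11 / -2.09 / -2.02 | 0.04 / -0.03 / -0.05 |
| 5 | 0 | -5 | -5.01 / -5.00 / -5.01 | -0.03 / -0.08 / 0.00 |
| 5 | 5 | 0 | 0.04 / -0.01 / 0.02 | 5.09 / 4.96 / 5.00 |
| 10 | 5 | -5 | -5.03 / -4.97 / -4.97 | 4.97 / 5.04 / 5.04 |

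The raw comparison recovers dL in every row. With d1 negative the sign reverses: d1 = -5 and dL = 0 gives 0 - (-5) = +5.

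**4. Covariate adjustment does not cure it.** With equal variances, adjusting for the day 5-7 score gives dL - correlation × d1. For d1 = 5 and dL = 5 this is 3.5, 2.5 and 1.5 at correlations 0.3, 0.5 and 0.7, instead of 5.

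**5. Which contrasts are exposed.** Groups 1 and 2 have the same first-week care, so d1 between them is expected to be 0 and tape versus brace is not biased. Only the contrasts with group 3 are.

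**The case against.** **Another reading of the sentence.** The bracketed phrase could attach to the VAS scores alone, and the models are also meant to estimate mean differences between groups. If Karlsson and FAOS were modelled raw with day 5-7 kept as a time point, that would be close to the remedy. This is possible, but the more natural reading covers all three scales. Even on the narrow reading, satisfaction has no baseline and the baseline for pain is left at the wrong visit or undefined.

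**A different but meaningful quantity.** Tape and brace start only after this visit, so change from day 5-7 describes the tape or brace phase, and the Objective is framed around those devices. That stands as far as it goes. The randomised strategies, however, include the bandage, and a comparison that conditions on its result is no longer a comparison of the strategies as randomised.

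**Limited exposure.** RICE and the exercise schedule are common to all arms, and group 3 may use an elastic sock, so the first-week difference may be small. This also stands; nothing in the article gives its size.

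**Stronger claims that a reader might infer.** One is that every later result is contaminated. It is not: the primary ANOVA uses the 6-month score, and recurrences and adverse events are analysed by chi-square or log-rank tests. Another is that the bias favours no support by some share of the 10-point margin. The article does not say which arm would be worse at 5-7 days. The Karlsson scale even gives 5 points to use of a support device; if a bandage counted there, which is not stated, the bandaged arms could score lower. The margin belongs to the primary ANOVA intervals and is not a yardstick for these models.

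**Conclusion.** The point holds for the secondary mixed models. As written, their comparisons of group 3 with groups 1 and 2 on Karlsson, FAOS and VAS pain equal the later difference minus a post-randomisation difference. The bias is one for one with any day 5-7 difference, of unknown size and direction, and zero if there is none. For VAS satisfaction the planned change cannot be computed.

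This rests on two readings of the article: that change from baseline applies to all three scales, and that baseline means the 5-7 day visit, the only one so labelled. The point values in the illustration are assumptions.

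The non-inferiority conclusion, the sample size, the recurrence and adverse-event analyses and the tape-versus-brace contrast do not depend on it. Because only secondary analyses are affected, this is a should-fix.

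**What to change.** - **Karlsson and FAOS:** model the raw scores with treatment, time and treatment-by-time. Treat day 5-7 as the first post-randomisation outcome; neither subtract it nor adjust for it. Report the group difference at each visit.
- **VAS pain:** use the <24 h value as the baseline covariate and treat day 5-7 as an outcome. Confirm that the <24 h value is recorded before allocated treatment starts, which the article does not state.
- **VAS satisfaction:** analyse the raw scores at 6 months and 1 year.
- **Trial design:** stop calling the 5-7 day visit baseline; first follow-up visit would be accurate.

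The cost is wording in two sections. Every measurement needed is already in Table 1, and the sample size and primary analysis stay as they are. The change should be made before the group data are examined.
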